#### Psychological, sleep, musculoskeletal and wellbeing outcomes

Perceived fatigue will be measured using the Chalder Fatigue Scale (58). Self-efficacy for reducing sitting will be assessed using an adapted version of the Schwarzer and Renner Physical Exercise Self-Efficacy Scale (59). A perceived sense of control over one’s actions and outcomes will be assessed using the Generalised Self-Efficacy Scale (60) and the Cohen Perceived Stress questionnaire will assess perceived stress (61). To assess the affective aspect of subjective wellbeing, the Positive and Negative Affect Scale will measure positive and negative mood (62, 63). The World Health Organization Five Well-Being Index will measure psychological wellbeing (64) and quality of life will be measured using the WHOQOL-BREF questionnaire (65). The Pittsburgh Sleep Quality Index questionnaire will assess sleep quality and duration (66) and musculoskeletal symptoms will be measured using the Standardised Nordic Questionnaire (67). These questionnaires will be completed online using an iPad provided to the participants following the above measures. The online questionnaires will be hosted by secure software, Qualtrics (Qualtrics, London, UK). See the questionnaires in supporting documents (Study questionnaires).

**COVID-19 contingency:** these questionnaire measures will be completed online or hard copy via post.

#### Physical function

This will be assessed using the Short Physical Performance Battery (SPPB) (68) and hand grip strength. The SPPB will be administered by trained researchers using standardised methods and includes assessment of standing balance, walking speed and rising from a chair. Standing balance will be tested using tandem, semi-tandem and side-by-side stands. For each stand type, the researcher will first demonstrate the task and will then support one arm while the participant positions their feet and then release support when the participant is ready and start timing. The timing is stopped when the feet move, the participant grasps the researcher for support or once 10 s has passed. For the semi-tandem stand, the heel of one foot (participant’s preference) is placed to the side of the first toe of the other foot. If unable to hold this position for 10 s, participants will be assessed with the feet in the side-by-side position. If the semi-tandem position is held for 10 s, participants will also be evaluated in the full tandem position with the heel of one foot directly in front of the toes of the other foot. Walking speed will be assessed using an 8-foot walking course with participants instructed to "walk to the other end of the course at your usual speed, just as if you were walking down the street to go to the store”. The walk is timed and is to be performed twice with the fastest used for analysis. For the chair stand (rising from a chair), a straight-backed chair will be placed next to a wall and participants will be instructed to fold their arms and stand up from the chair once. If they perform this successfully, the participants will be asked to stand up and sit down as quickly as possibly five times, which will be timed. Each of the SPPB assessments are scored on a 0-4 scale following published guidelines (68).

Grip strength will be measured on the dominant hand using a digital hand grip dynamometer (Takei Scientific Instruments Co.,Ltd, Yashorida, Japan) while in a standing position with the shoulder adducted and neutrally rotated and elbow in full extension. Three maximum attempts will be performed with a 1-min rest between each and the average recorded (69).

**COVID-19 contingency:** For the standing balance test, participants will be advised to do this next to a table for support in replace of the research assistant giving balance support. For walking speed, participants will be asked to identify an 8-foot clear space where they can perform the test. They will be provided with an 8-foot cardboard foldout ruler to mark out the distance. The chair sit to stand task will be performed at home if the participant has an appropriate chair that can be positioned steady against a wall. All of these tests will be completed during a Zoom video call between the participants and research assistant. The sessions will be recorded so that the research assistant can deduct the time taken to complete each test. Grip strength will not be measured.

#### Process evaluation and intervention acceptability

Process evaluation questionnaires will be completed by every participant (see Process evaluation questionnaires) and semi-structured one-to-one interviews (see Intervention and Control participant interview scripts) will be completed with intervention participants until saturation is reached. Interviews will be conducted by video call or phone if needed due to the pandemic. Interviews will aim to evaluate acceptability of the intervention including compliance with intervention components, facilitators and barriers to participation/compliance, choices made regarding the self-selected behaviour change tools, in addition to evaluating intervention fidelity. The APEASE criteria of the Behaviour Change Wheel (70) will be used to specifically uncover Affordability (Can it be delivered to budget?), Practicability (Can it be delivered as designed?), Effectiveness and cost-effectiveness (Does it work, is it cost-effective?), Acceptability (Is it judged appropriate by relevant stakeholders?), Side-effects/safety (Does it have any unwanted side-effects or unintended consequences?), and Equity (Will it reduce or increase the disparities in health/wellbeing and can it be accessed without causing disparity?). Each intervention strategy and BCT will be scored for each of the APEASE criteria (71). The research team will record completion rates for the online programme, number of face-to-face and telephone health coaching sessions, the number of times each self-selected behaviour change tool is chosen, the combinations in which they are chosen, switches in these tools made during the intervention and reasons for the switches. Interviews will also assess suitability of data collection procedures with participants (mix of control and intervention) until saturation is reached. A sample size of 13 is recommended for theory-based interview studies as this number of participants has been found to capture 97% of important codes from a total of 60 interviews (72); therefore we will aim for approximately this number. Semi-structured video call or phone interviews with all health coaches will assess the feasibility of delivering the coaching sessions (see Health coach interview script). Coaches will be asked to audio record 30% of their sessions, which will be coded using the list of BCTs included in the trial and the Motivational Interviewing Treatment Integrity scale (73) to assess fidelity. Coders will also listen out for any additional (unintended) BCTs they may have been used not in the protocol. Interviews will be recorded using Otter (which is an automatic transcription app that syncs data over an encrypted connection) in addition to an encrypted dictaphone as backup.

### Data analysis

#### Eligibility, recruitment, retention and outcome measure rates

This will include calculating eligibility ([participants eligible / participants assessed for eligibility] x 100), referral ([potentially eligible participants at recruitment sites / number of participants referred] x 100) recruitment ([participants randomised / number of eligible participants screened] x 100) and retention ([participants completing the intervention / participants enrolled] x 100) rates in addition to completion rates for the data collection measures ([participants providing full outcome data / participants completing the study] x 100). The number of participants recruited via the different recruitment strategies and reasons for ineligibility and withdrawal (including if none of the self-selected behaviour change tools are suitable to an individual’s need) will also be evaluated. Suitability of the data collection procedures will be evaluated via missing data rates and as part of the semi-structured interviews described above.

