## RESEARCH OBJECTIVES

The main objectives of this feasibility study are to:

1. Establish and refine a recruitment strategy for people with Type 2 diabetes.
2. Determine participant attrition in the trial.
3. Determine completion rates for outcome measures (and whether these are sufficiently high to provide accurate data in a full trial).
4. Assess the acceptability of randomisation to the intervention and usual care.
5. Assess the acceptability of the intervention and data collection to participants.
6. Assess intervention fidelity and adherence.
7. Explore the feasibility of collecting data (as below) to inform the design of the health economics component in a full RCT.

The secondary objectives are to derive preliminary estimates of the effect of the intervention on participants’:

1. Device measured daily sitting time, prolonged sitting time, breaks from sitting and light and moderate-to-vigorous physical activity.
2. Cardiometabolic risk markers (BMI, waist circumference, body fat%, fasting glucose, glycated haemoglobin, lipids, blood pressure)
3. Fatigue, self-efficacy for reducing sitting time, psychological wellbeing, mood, physical functioning, musculoskeletal symptoms and quality of life.

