### Recruitment

Participant recruitment will be via GPs where study information will be sent out via postage using Docmail and via the GP Practice SMS text messaging service (see Docmail GP invitation letter and SMS content in additional files) to potentially eligible patients using a database search. The GP invitation letter will also be provided during consultations if the GP or nurse considers their patient to be potentially eligible. All NHS recruitment is being supported by the London North West local Clinical Research Network. This is in addition to recruiting via local Diabetes UK support groups (via email send out of the Participant Information Sheet and attendance at group sessions) and social media (including a video professionally developed by Health & Care Innovations; the script for this is based on information from the PIS). A link to the video will also be accessible from the project webpage ([tinyurl.com/RESIT-information](https://tinyurl.com/RESIT-information)), which is another route that potentially eligible participants may find information about the study. Participants recruited via these latter routes will be mapped back to their GP Practice. Potentially eligible participants will be asked to express their interest by email, returning a reply slip to the research team, or by scanning a QR code provided on recruitment materials to pass their name and email address (via Qualtrics) to the research team. A researcher will then contact interested volunteers by email/telephone to screen them. Individuals who remain potentially eligible will then be invited to complete baseline data collection after providing informed consent.

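### The referral rate is defined with numerator and denominator reversed, so for a fixed pool it rises as fewer people are referred

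*Protocol*

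**What the plan says.** The Protocol's Data analysis section, under the heading on eligibility, recruitment, retention and outcome measure rates, gives five rates in one sentence. One is "referral ([potentially eligible participants at recruitment sites / number of participants referred] x 100". The other four are "eligibility ([participants eligible / participants assessed for eligibility] x 100", "recruitment ([participants randomised / number of eligible participants screened] x 100", "retention ([participants completing the intervention / participants enrolled] x 100" and, for completion of the measures, "participants providing full outcome data / participants completing the study] x 100".

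These rates bear on main objective 1 in Research objectives: "Establish and refine a recruitment strategy for people with Type 2 diabetes".

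The Recruitment section describes the steps being measured. Study information goes by post and text message "to potentially eligible patients using a database search", and a GP or nurse may hand over the invitation letter in a consultation. Diabetes UK support groups, social media and a project webpage are further routes, and people who come that way are traced to their GP practice. The next step is the patient's own: "Potentially eligible participants will be asked to express their interest by email, returning a reply slip to the research team", or a scanned QR code. The section does not say which of these steps makes someone 'referred', and neither does the rest of the Protocol.

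**The concern.** A referral rate should say what share of the people who could have been referred were referred. The printed fraction gives the reciprocal: the number potentially eligible per person referred, expressed as a percentage. An analyst who follows the text will report a figure that moves the wrong way, with a high value meaning little referral and a low value meaning much.

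In a feasibility trial the process rates are main results, and this one informs the first main objective. A figure in the hundreds of per cent beside four ordinary percentages would at best puzzle readers. At worst it would be carried into the planning of a full trial as though a larger value were better.

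**Working it through.** **Inputs.** The formula and the four comparison rates come from the Data analysis section of the Protocol. The Protocol gives no referral counts and no expected referral rate, so there is no stated figure to reproduce. Let E be the number potentially eligible at recruitment sites and R the number referred. All values of E and R below are assumed.

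**Step 1: direction of the five rates.**

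| Rate | Top | Bottom | Form |
|---|---|---|---|
| Eligibility | eligible | assessed | subset / pool |
| Recruitment | randomised | eligible and screened | subset / pool |
| Retention | completers | enrolled | subset / pool |
| Completion of measures | full data | study completers | subset / pool |
| Referral | potentially eligible at sites | referred | pool / subset |

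Only referral is reversed.

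**Step 2: behaviour of the stated formula.** As written, rate = 100 × E / R. With E fixed, the rate falls as R rises. If everyone referred comes from the site pool, then R ≤ E and 100 × E / R ≥ 100, with equality only when the whole pool is referred.

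**Step 3: illustration with assumed counts.**

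| E | R | As written, 100 × E / R | Swapped, 100 × R / E |
|---|---|---|---|
| 400 | 120 | 333% | 30% |
| 400 | 40 | 1000% | 10% |
| 500 | 50 | 1000% | 10% |
| 500 | 250 | 200% | 50% |
| 500 | 500 | 100% | 100% |

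With E = 400, cutting referrals from 120 to 40 takes the stated rate from 333% to 1000%, while the share referred falls from 30% to 10%.

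**Step 4: what happens if R is not drawn from E.** If some of those referred lie outside the site pool, R can exceed E. With E = 500 and R = 520, the stated rate is 100 × 500 / 520 = 96.2%, and the swapped rate is 100 × 520 / 500 = 104%. The floor of 100% in Step 2 is therefore conditional. Swapping the terms alone also does not guarantee a proportion; 'referred' has to be defined so that R is counted within E.

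**The case against.** **The order may be intended.** The fraction could be read as the share of referred people who prove potentially eligible. The words fit this poorly. The top line is counted at recruitment sites, and in the Recruitment section the potentially eligible are the patients found by database search before any contact, not people assessed after referral. That reading would also largely repeat the eligibility rate. It does not stand.

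**The slip does little harm.** It is one descriptive rate among several. The Protocol ties no progression criterion, sample size or effect summary to it. Both counts are needed in either direction, so no data are lost and the correct value can be recovered from the reciprocal. A printed 333% would probably be noticed. All of this stands, and it is why the point is minor.

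**Stronger readings a reader might infer.**

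- That the rate is always at least 100%. This needs those referred to be a subset of the site pool. People arriving through Diabetes UK groups or social media may fall outside the database search, and the Protocol does not say how they are counted.
- That poorly referring practices would be ranked above good ones. No comparison of practices on this rate is planned; the planned breakdown is the number recruited by each strategy.
- That the plan is deficient because it has no rate of response per invitation. That would be an additional measure, which may be set out elsewhere, and its absence is not an arithmetic error. The Protocol also gives no figures for losses at each step, so it cannot be said where most people drop out.

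**Conclusion.** The referral rate is wrong as written. The reversal is plain beside the four neighbouring rates, and no other part of the Protocol puts it right. That it moves the wrong way holds for any fixed pool. That it cannot go below 100% holds only when those referred come from the site pool. The size of the distortion depends on counts the Protocol does not give; 333% against 30% is an illustration from assumed numbers.

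The severity is minor. One descriptive feasibility measure under main objective 1 is affected. The other four rates run in the right direction, and nothing in the sample size or the summaries of preliminary effect depends on this one.

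**What to change.** Restate the rate as: referral = (number of participants referred / potentially eligible participants at recruitment sites) × 100.

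Add a sentence saying who counts as referred under each route in the Recruitment section. Keep this distinct from merely being sent an invitation. Study information is sent to the potentially eligible patients found by the search, so counting everyone invited would put the rate near 100% by construction on that route. Say also whether people recruited through Diabetes UK groups and social media are counted. If they are, include them in both terms or report them separately, so that the result remains a proportion.

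The cost is a line or two of wording. Participant procedures do not change, and the two counts are those the existing formula already requires, once 'referred' is defined.

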### Sample size

Sample sizes between 24 and 50 have been recommended for feasibility studies (46, 47). A sample size of 70 will be used in this study (n=35 in each the intervention and control groups) to allow for the different combination of intervention tools that the participants are able to select from and to allow for drop out.

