### Randomisation

Eligible participants will be randomised by an independent researcher in a 1:1 (intervention:control) ratio using a fixed block size of 4. Block randomisation is used to increase the likelihood of achieving balance of numbers in the allocation to groups given the relatively small sample size, i.e. each aim is more likely to contain an equal number of individuals.

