These tools will be provided to participants (face-to-face or via post) or downloaded onto their phone/computer under guidance from the research assistant following completion of the online programme. Participants will be permitted to choose a maximum of one tool from each of these categories (e.g. one smartphone app, one computer prompt, one wearable device or paper-based tracker) but they are not required to choose a tool from every category. For example, a participant may choose a smartphone app and a wearable device only. The choice is theirs, thus making the intervention person-focused to increase potential effectiveness. This is consistent with Self-Determination Theory and accepted ways of boosting intrinsic motivation. The research assistant will provide a guidance document to the participant for each tool selected that will explain how to download and how it works. Participants will not receive any instructions on how often they should engage with the tools that they select given that the intervention is person-focused. The self-selected behaviour change tools used can be changed during the intervention period if a participant reports to the health coach or research team that they are not engaging with the tool. This might be due to reasons such as technical complexity, impracticality or a dislike of the tool. If there are any problems with using any of the tools during the intervention, participants will be able to contact the research assistant for troubleshooting.

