### Control group

Participants randomised to this group will receive usual care. They will complete the same measurements as the intervention group. After the trial has concluded, they will be offered use of the psychoeducation programme and the self-selected behaviour change tools.

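### The retention rate counts people who complete the intervention, which does not fit the usual-care arm and does not measure attrition in the trial

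*Protocol*

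**What the plan says.** The Data analysis subsection on eligibility, recruitment, retention and outcome measure rates gives a formula for each feasibility rate. For retention it is "retention ([participants completing the intervention / participants enrolled] x 100". It is not restricted to one arm. The recruitment rate in the same sentence counts people randomised. The outcome completion rate, also in that sentence, has as its denominator those who finish the study, which is a different term from finishing the intervention. Reasons for withdrawal and missing data rates are to be evaluated too, but without a formula.

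The Research objectives section lists as a main objective to "Determine participant attrition in the trial". Intervention fidelity and adherence form a separate main objective.

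The Control group section states: "Participants randomised to this group will receive usual care". It adds: "They will complete the same measurements as the intervention group". Controls are offered parts of the intervention only later: "After the trial has concluded, they will be offered use of the psychoeducation programme and the self-selected behaviour change tools".

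The Sample size section states: "A sample size of 70 will be used in this study (n=35 in each the intervention and control groups"). Randomisation is "in a 1:1 (intervention:control) ratio using a fixed block size of 4".

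**The concern.** Attrition is a property of the whole trial: how many of those randomised, in each arm, are still being measured at follow-up. The stated numerator is a property of the intervention, and half the participants are not given it. A control participant who attends every visit has completed no intervention, and one who disappears after baseline has completed no intervention either. Read literally, the formula treats the two alike.

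In the intervention arm the numerator also runs adherence together with follow-up, and the protocol sets no threshold for having completed the intervention. For the tools, "Participants will not receive any instructions on how often they should engage with the tools that they select". The online programme and the coaching sessions are recorded, but no number of them is named as completion.

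The denominator raises a further question. The Confidentiality and record keeping section treats consent as entry to the study. Under Recruitment, consent comes before baseline measurement. Under Participants, a baseline fasting glucose below 7 mmol/L leads to exclusion, and Study design places randomisation after baseline. Someone who consented and was excluded at baseline may therefore count as enrolled without ever being randomised.

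At stake is a main result of a feasibility study. The Sample size section allows for dropout but gives no rate, so a full trial would naturally look to this one for an estimate.

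**Working it through.** **Inputs.** Total 70, 35 per arm (Sample size). Allocation 1:1 in blocks of 4 (Randomisation). No intervention for controls during the trial, but the same measurements (Control group). The protocol states no expected or target retention, so there is no such figure to reproduce. The arm sizes agree with the total: 35 + 35 = 70.

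**Ceiling under the literal reading.** Only the intervention arm can contribute to the numerator, so the maximum is intervention-arm size / total enrolled × 100.

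- Equal arms: 35/70 = 50.0%.
- 70/4 = 17.5, so the last block is half filled. The 17 full blocks give 34 per arm, and the last two participants may fall either way. The arms can therefore be 34 to 36: 34/70 = 48.6%, 36/70 = 51.4%.

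**Response to control-arm loss under the literal reading.** Hold intervention completers at 30 of 35, assume that those 30 are also the ones followed up, and vary the number of controls who finish (all assumed counts, for illustration):

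| Controls finishing | Stated rate | Followed up / randomised |
|---|---|---|
| 35 | 30/70 = 42.9% | 65/70 = 92.9% |
| 28 | 30/70 = 42.9% | 58/70 = 82.9% |
| 20 | 30/70 = 42.9% | 50/70 = 71.4% |

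The stated rate does not move.

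**Denominator.** Suppose enrolled means consented and a share x is excluded at baseline before 70 are randomised. Then enrolled = 70/(1 − x), and the literal ceiling is 35 × (1 − x)/70. For assumed x of 10%, 20% and 30% this is 45%, 40% and 35%. The documents give no value for x. Under the COVID-19 contingency, where glucose may not be measured, this route of exclusion would not operate.

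**Other readings of the formula.**

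- Denominator restricted to the intervention arm: the maximum is 35/35 = 100%, but the rate is then intervention completion, which belongs to the adherence objective.
- Numerator read as completing the 24-week period in either arm: the maximum is 70/70 = 100%, and the rate comes close to trial retention, subject to the meaning of enrolled.

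**Whether another defined rate fills the gap.** The outcome completion rate is conditional on finishing the study. A control participant lost to follow-up leaves its denominator and so does not count against it. Withdrawal is covered by reasons, not by a rate. Missing data rates are mentioned without a definition, as a way to judge the data collection procedures.

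**The case against.** The strongest reply is that the formula is only loosely worded. The Study design section says that after randomisation to either condition an intervention period of 24 weeks begins, with the last follow-up at 24 weeks. That describes the period for the trial as a whole. Completing the intervention could then mean reaching the end of that period in either arm. Controls would have a value and there would be no ceiling. This reading is possible, and for that reason the 50% figure should not be taken as a fixed property of the plan. It is not stated, however, and the use of a separate term for finishing the study in the same sentence counts against it.

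A second reply is that no information is lost. Both arms are measured at baseline, 12 and 24 weeks, and reasons for withdrawal are evaluated. This stands. A reader might infer that the plan conceals a difference in attrition between arms, but losses by arm can be derived directly from the collected data. What is wrong is the rate, not the data behind it.

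A reader might also infer that someone who gives up the tools but attends at 24 weeks is counted as lost. The documents do not support this. They do not say what completion is, they let participants change tools, and they do not tie completion to tool use. How such a person would be classified is unknown.

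Finally, the missing completion threshold could be set in a statistical analysis plan that is not at hand. That is fair, and the point does not rest on it. A threshold would still leave the control arm without a value under the literal reading.

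**Conclusion.** The point holds as an error of definition. The protocol fixes a retention formula that does not suit a trial with a usual-care arm and does not measure the attrition named among its main objectives. None of the other defined rates does so.

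The size depends on the reading. Taken literally, with 70 enrolled and equal arms, the rate tops out at 50% (48.6% to 51.4% with arms of 34 to 36), lower still if enrolled includes people excluded at baseline, and it ignores control-arm loss altogether. Taken as completion of the 24-week period in both arms, there is no ceiling, and what remains is unclear wording. It would go beyond the documents to say that the reported retention is bound to be about half the true figure.

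The plan states no progression criterion, sample size calculation or test that uses this rate, and the data needed for a correct one are already to be collected. It should be fixed, but it is not a fault that undermines the trial.

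**What to change.** Replace the retention formula with a rate at each follow-up visit, stated separately for 12 weeks and for 24 weeks: participants attending or providing follow-up data at that visit, divided by participants randomised, × 100, overall and by arm. State that people who stop the intervention but are measured at the visit count as retained.

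Report intervention completion as a separate adherence rate in the intervention arm only, with those randomised to the intervention as denominator. The records of online programme completion and coaching sessions described under Process evaluation and intervention acceptability can supply it.

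The cost is one paragraph of protocol wording. No new data, visits or procedures are needed.

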#### Body composition

This will be measured via body mass index (BMI), waist circumference and body fat% using bioelectrical impedance analysis. Height will be measured to the nearest 0.1 cm using a stadiometer (Seca 222, Seca Ltd, Birmingham, UK) with participants standing upright looking forwards, heels on the floor and feet together. Weight and body fat% will be measured using electronic weighing scales and bio-electrical impedance analysis (BIA) with the TANITA MC-780MA P segmental body composition analyzer (Tanita Corp., Tokyo, Japan). Participants will wear light clothing and remove shoes and socks for this measurement. This device produces valid and reliable body fat estimations in adults (57). BMI will be calculated as weight (kg) / height^2^ (cm). Waist circumference will be measured using an adjustable tape measure (Seca 201, Seca Ltd, Birmingham, UK) to the nearest 0.1 cm midway between the lowest rib and the iliac crest at the end of gentle expiration.

**COVID-19 contingency:** Participants will be asked to self-report their waist circumference at each relevant time point. They will be provided with a tape measure and written guidance on how to take this measure. Body fat %, height and weight measures will not be taken.

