#### Cardiometabolic risk markers

Glycated haemoglobin will be measured using the Quo-Test HbA1c Analyzer (EKF Diagnostics, Cardiff, UK). Fasting total cholesterol, HDL, triglycerides and glucose will be measured using the CardioChek PA point-of-care-system (PTS Diagnostics, Indianapolis, Indiana). A finger prick sample technique will be used to collect capillary blood for these measures. Blood pressure will be measured on the right arm in a seated position using an Omron M5-I automatic monitoring device (Omron Matsusaka Co Ltd, Matsusaka, Japan). After 5 min of rest, the first reading will be taken with a further two readings taken with a 2 min rest between each. The average of the lowest two recordings will be used for analysis.

**COVID-19 contingency:** these measures will not be taken if it is not possible or safe to collect face-to-face data from participants.

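### The outcome completion rate is taken among study completers, so it overstates data yield among those randomised, and full data is left undefined where the COVID-19 contingency drops measures

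*Protocol*

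**What the plan says.** Main objective 3 (Research objectives) is to "Determine completion rates for outcome measures (and whether these are sufficiently high to provide accurate data in a full trial". The statistic that answers it is in Data analysis, under eligibility, recruitment, retention and outcome measure rates. That section plans "completion rates for the data collection measures" and defines them as "participants providing full outcome data / participants completing the study] x 100".

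Two neighbouring statements bear on this. Retention is a separate rate: "retention ([participants completing the intervention / participants enrolled] x 100". The section also says: "Suitability of the data collection procedures will be evaluated via missing data rates". No denominator is given for those missing data rates.

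The Data collection section plans measures at baseline, 12 and 24 weeks and sets a COVID-19 contingency for each measure:

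- Cardiometabolic markers: "these measures will not be taken if it is not possible or safe to collect face-to-face data from participants".
- Body composition: "Body fat %, height and weight measures will not be taken". Waist circumference stays, by self-report.
- Physical function: "Grip strength will not be measured". The SPPB tests stay, at home by video call.
- activPAL and questionnaires stay, by post or online.

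The protocol does not say how a measure withdrawn in this way counts towards full outcome data.

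**The concern.** A full trial is sized on how many randomised participants will contribute the outcome. A rate taken among completers answers a narrower question: of those who stayed, how many gave everything? It can stay high however many people leave. If it is read as the answer to objective 3, the full trial would be planned on too favourable a yield.

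The second difficulty lies in the numerator. Study design says the trial will probably run under pandemic conditions, so remote collection is an expected scenario. Without a rule for measures that were never offered, a reader cannot tell whether a low rate means that participants failed to complete measures or that the team did not take them.

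**Working it through.** **Inputs.** N = 70 randomised (Sample size). The same section allows for dropout but states no rate, so the dropout values below are assumptions. So is the level of about 90% completeness among completers. C is the number completing the study and F the number with full data. F is taken to be a subset of C. The protocol states no completion figure, so there is none to reproduce.

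**Denominator.**

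- Rate by the protocol's formula: F/C.
- Yield among randomised: F/N = (F/C) × (C/N).
- Ratio of the first to the second: N/C = 1/(1 − dropout).

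The ratio is 1/0.9 = 1.11 at 10% dropout, 1/0.8 = 1.25 at 20% and 1/0.7 = 1.43 at 30%. With counts rounded to whole participants:

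| Assumed dropout | C | F | F/C | F/70 | Gap (points) |
|---|---|---|---|---|---|
| 0% | 70 | 63 | 90.0% | 90.0% | 0.0 |
| 10% | 63 | 57 | 90.5% | 81.4% | 9.0 |
| 20% | 56 | 50 | 89.3% | 71.4% | 17.9 |
| 30% | 49 | 44 | 89.8% | 62.9% | 26.9 |

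The protocol's rate stays near 90% while the yield falls by 27 points.

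**Can retention recover the yield?** Retention is I/E, where I is the number completing the intervention and E the number enrolled. The product (F/C) × (I/E) equals F/N only if I = C and E = N. The first condition is doubtful. The numerator of retention is completion of the intervention, the denominator of the completion rate is completion of the study, and the control group receives usual care, so it has no intervention to complete. The second depends on what enrolled means, which this section does not define.

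**Full data under the contingency.** There are two readings.

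1. *One composite of all planned measures.* A participant measured remotely cannot qualify. Assume 56 completers and 90% completeness in person:
   - none remote: 50/56 = 89.3%
   - a quarter remote (14): 38 of the 42 measured in person, 38/56 = 67.9%
   - half remote (28): 25 of the 28 measured in person, 25/56 = 44.6%
   - all remote: 0/56 = 0%

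   Participant behaviour is the same in every row; only the collection mode changes.
2. *One rate per measure.* Only the withdrawn measures are affected. activPAL sitting time, the questionnaires, waist and SPPB keep ordinary rates.

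The completer denominator applies under both readings.

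**The case against.** The best defence is that attrition is not hidden. Determining it is main objective 2, retention and reasons for withdrawal are reported beside completion, and separating who stayed from how complete their data were is a legitimate decomposition. The numbers randomised and the numbers with full data are already to be counted, so the yield could be worked out later. This stands as mitigation. It is not a repair, because the two published rates do not multiply to the yield and the formula tied to objective 3 is the completer one.

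It is also fair that the size rests on assumed dropout and completeness. The table shows what the formula does across a range, not what this trial will observe.

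Three stronger readings are tempting, and the protocol does not support them:

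- *The contingency forces the rate to 0%.* That needs the composite reading and every completer missing a withdrawn measure. The text speaks of rates and measures in the plural, which permits a rate per measure, and the contingency is conditional.
- *No single-measure rate will be available.* The plural wording and the planned missing data rates leave room for one.
- *Requiring full data adds to the overstatement.* It works the other way: a stricter numerator lowers the rate. Only the completer denominator raises it.

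A threshold for a sufficient rate, a headline outcome, rates by arm and confidence intervals are separate matters. This point does not depend on them.

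**Conclusion.** The concern holds in two parts. First, the completion rate is conditioned on completing the study and so exceeds the share of randomised participants who yield data whenever there is dropout and at least one participant has full data. The inflation factor is 1.11 to 1.43 for assumed dropout of 10% to 30%, and 1.00 with none. This does not depend on how full data is read. Second, full outcome data is not reconciled with the contingency. On a composite reading the rate would track the share of remote visits; on a per-measure reading the retained measures, including the activPAL primary outcome, are unaffected. The defect here is that the protocol does not fix which reading applies.

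The rate is descriptive and no hypothesis test depends on it. It matters because it is the defined answer to a main objective, and it can be corrected from counts that are already planned.

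**What to change.** Replace the formula with, for each measure and each time point, participants with a usable value divided by participants randomised. The completer-based rate may stay as a supplement if it is labelled as such.

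For measures withdrawn under the contingency, take the affected participants out of that measure's denominator at that visit and report them as not offered, separately from those who were offered the measure but have no value. For participants who left before a visit, state how their mode is assigned, for instance by the mode in force when the visit was due.

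The cost is a change of protocol wording and one collection-mode flag per visit. No additional participant measurements are needed. The reported rate will look less favourable.
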